### Data management {19}

Rehabkompassen will collect PROM data automatically, which will be kept securely in electronic form in the Region of Västerbotten with regular backups. Baseline data collection will be carried out by using REDCap, hosted at Umeå University. REDCap [19] is a secure, web-based software platform designed to support data capture for research studies. It provides several functions, such as (1) an intuitive interface for validated data capture; (2) audit trails for tracking data manipulation and export procedures; (3) automated export procedures for seamless data downloads to common statistical software packages; and (4) procedures for data integration and interoperability with external sources [19]. All data will be coded with a study number, the participant’s initials and the participant’s date of birth. Paper coding files will be stored in a secure location at each site. A separate data management plan for the study is kept at Umeå University.

### Confidentiality {27}

All study personnel will endeavour to protect the rights of the participants to privacy and informed consent. All information collected will be treated confidentially in accordance with the consent provided, adhering to the EU data protection rules (https://ec.europa.eu/info/law/law-topic/data-protection/eu-data-protection-rules_en). No outsider will be able to access the database. All analyses will take place at the group level where no individuals can be identified. Upon study completion, the data will be transferred from Redcap to Umeå University in an encrypted format and stored for at least 10 years together with data from Rehabkompassen®.

### Plans for collection, laboratory evaluation and storage of biological specimens for genetic or molecular analysis in this trial/future use {33}

This is not applicable as no biological specimens will be collected.

## Statistical methods

### Statistical methods for primary and secondary outcomes {20a}

Group differences in the mRS and SIS-p scores at the 12-month follow-up will be tested using ordinal logistic (proportional odds) regression, adjusted for site with fixed effects [43]. For the SIS-p score, models will also be adjusted for the baseline SIS-p score, with natural cubic splines to account for nonlinearity in the association. The results from the analyses will be presented as odds ratios with corresponding 95% confidence intervals and *p* values.

For the two primary outcomes, adjustments of the significance levels of the individual tests will be performed using the Holm–Bonferroni method to ensure that the familywise error rate will not be inflated above 0.05.

Secondary outcomes on an ordinal scale will be analysed similarly using ordinal logistic regression. All analyses will primarily be conducted in accordance with the intention-to-treat principle. As complementary analyses, per-protocol analyses will be performed using data from patients with full availability of primary variables and predefined criteria for adherence. Further details about the statistical analyses will be predefined and published in a separate statistical analysis plan. A data management plan has been established, providing details of the handling, organization and storage of study data.

A statistical significance level of *p* < 0.05 (two-tailed) will be applied to all analyses. For the two primary outcomes, adjustments of the significance levels of the individual tests will be performed using the Holm–Bonferroni method to ensure that the familywise error rate will not be inflated above 0.05.

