### Outcomes {12}

Participants’ demographic data (e.g. age, sex, comorbidities, stroke characteristics and severity) will be obtained via REDCap or from the Swedish Stroke Register (Riksstroke) at the first visit (T1 in Table 1). All data and outcomes collected by ePROMs will be in Swedish, which is the official language in Sweden.

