#### Primary outcome

We will use two primary outcomes consisting of the smRSq [20–24] and Domain 8 of the SIS (SIS-D8) [25] since the smRSq covers daily activity and the SIS-Ds assesses social participation. This is because the smRSq, as a single primary outcome, is often not sensitive enough to capture the subtle alterations of treatment effects on stroke survivors [11, 21, 26]. Furthermore, our pilot study and previous Swedish stroke RCTs have demonstrated that most of the target study population has more limitations in social participation due to mild to moderate disability [11, 21, 27]. Domain 8 in the SIS (SIS-D8) [25] will thus be used as another primary outcome to capture the minor but important changes in social participation. Both primary outcomes will be reported by all patient-participants at the 3- and 12-month visits (Table 1). The time points for measurement of the primary outcomes will only be at 12 months after the occurrence of the stroke.

*Primary outcome: The smRSq* [20, 21] covers patients’ independence/disability levels in their daily activities. It is based on yes/no responses to five questions, which is summed into a seven-category total score (taking values from 0 to 6). An smRSq score of 0–2 (from no symptoms to independent but with a minor disability) will be considered a favourable outcome. A poor outcome will be considered as an smRSq score of 3–5 (from disability but able to walk to bed-bound and in need of full nursing care) or 6 (death). smRSq scores of 6 will be collected from patients’ medical records. The smRSq has shown good reliability among stroke survivors [20].

*Primary outcome: Domain 8 in the SIS (SIS-D8)* [25] assesses social participation (SIS-p), such as work and social activities. Social participation is the dominant problem among persons after stroke, as reported in previous Swedish stroke RCTs [21], but is not covered by the smRSq. The SIS-D8 will result in an ordinal score measuring social participation that ranges from 0 to 100. A higher score indicates a lower impact of stroke [28]. The SIS has demonstrated great internal consistency and construct validity in the stroke population [28, 29].

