### Sample size {14}

The study is predicted to have 90% power in the analysis of both primary outcomes at a significance level of 2.5% for each individual test to account for planned correction for multiple comparisons with a target familywise error rate of 5%.

Sample size calculations were performed assuming a mean difference of 4 points in the SIS-p score between the groups at the 12-month follow-up. There is uncertainty regarding the minimum clinically important difference in the SIS-p, but differences in sizes between 10 and 15 points have previously been suggested [29]. A power analysis was conducted using Monte Carlo simulations, in which SIS-p data for the control group were generated from a beta distribution with *α* = 1.1 and *β* = 0.5, while Rehabkompassen® data were generated under the assumption of *α* = 1.1 and *β* = 0.385. This corresponds approximately to a mean value of 70 and a standard deviation of 28 for the control group, in line with what Guidetti et al. [25] reported for a population of stroke patients at 12 months after stroke. Under these assumptions, the results showed that we need to include 940 patients to detect a statistically significant difference in the SIS-p score when using an ordinal proportional odds model to compare the groups at the 12-month follow-up. The average odds ratio across all simulations was 1.5, as estimated using the function *orm* from the R package *rms* for comparing the intervention group to the control group [40]*.*

The sample size calculation for the mRS score was based on aggregated unpublished data from the Swedish Stroke Register (Riksstroke). The marginal distribution of mRS scores collected 12 months after stroke among Swedish patients was *0: 22.4%*, *1: 18.0%*, *2: 18.0%*, *3: 16.8%*, *4: 11.1%*, *5: 4.3%* and *6: 9.4%*. The function *popower* from the package *Hmisc* [41] in the statistical software R was used to determine that a sample size of 940 patients (470 in each group) is sufficient to detect a true odds ratio of 0.67 at 90% power when using an ordinal proportional odds model to compare groups.

Thus, 940 patients should be sufficient for both primary outcomes. To account for a 15% loss to follow-up rate, we plan to recruit 1106 patients for the study (Fig. 3).

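### The primary smRSq model leaves out the first-visit smRSq, although the SIS-p model adjusts for its own baseline and both are collected in both arms

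*Protocol article*

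**What the plan says.** The section Statistical methods for primary and secondary outcomes {20a} analyses both primary outcomes (the smRSq appears there as mRS) at 12 months by "ordinal logistic (proportional odds) regression, adjusted for site with fixed effects". The next sentence adds a covariate for one of them: "For the SIS-p score, models will also be adjusted for the baseline SIS-p score, with natural cubic splines". No baseline term is named for the smRSq.

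The value needed for such a term is collected. Under Primary outcome: "Both primary outcomes will be reported by all patient-participants at the 3- and 12-month visits". Participant timeline {13} designates first-visit data as the baseline for the statistical analyses.

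Sample size {14} sets the target for the smRSq: "a sample size of 940 patients (470 in each group) is sufficient to detect a true odds ratio of 0.67 at 90% power", tested "at a significance level of 2.5% for each individual test to account for planned correction for multiple comparisons".

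**The concern.** First-visit disability would be expected to predict disability at 12 months. The plan uses this kind of information for SIS-p and not for smRSq, with no explanation, although the two outcomes are collected from the same people at the same visits and share the familywise error rate.

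Two things are at stake. The first is precision: a prognostic covariate already in the database is left unused on one of the two primary tests, in a trial whose Discussion calls recruiting more than 1000 patients a major challenge. The second is chance imbalance: Sequence generation {16a} stratifies by clinic only, so a difference between arms in first-visit disability would go uncorrected in the smRSq analysis but not, for its own baseline, in the SIS-p analysis.

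**Working it through.** **Inputs from the protocol article.** Two-sided alpha 0.025 per primary test, 940 evaluable patients (470 per arm), odds ratio 0.67, and the 12-month mRS distribution 22.4, 18.0, 18.0, 16.8, 11.1, 4.3 and 9.4% for scores 0 to 6 (sum 100%), all from Sample size {14}; two-sidedness from section {20a}. **Assumed:** the correlation r between first-visit and 12-month smRSq, taken from 0.3 to 0.7 because the documents give none.

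**Step 1: reproduce the stated figure.** The Whitehead formula for a two-group proportional odds comparison is

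V = n1·n2·n / [3(n+1)²] × (1 − Σp³), power = Φ(|ln OR|·√V − z), with z = 2.241 at two-sided alpha 0.025.

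- Σp³ = 0.0299, so 1 − Σp³ = 0.9701.
- V = 470 × 470 × 940 / (3 × 941²) × 0.9701 = 75.83, and √V = 8.708.
- OR 0.67: 0.4005 × 8.708 = 3.487; Φ(3.487 − 2.241) = 89.4%.
- OR 1/1.5: 0.4055 × 8.708 = 3.531; Φ(3.531 − 2.241) = 90.1%.
- N for 90% power at OR 0.67: 12 × (2.241 + 1.282)² / (0.4005² × 0.9701) = 957; at OR 1/1.5 it is 934.
- Loss to follow-up: 940 / 0.85 = 1106.

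At alpha 0.05 the power would be 93.7%, so alpha 0.025 was indeed used. The stated 940 and 90% therefore come from a comparison with no baseline covariate, and they hold on that basis.

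**Step 2: add baseline smRSq, by approximation.** A covariate correlated r with the outcome scales the required sample by about 1 − r². The test statistic at N = 940 becomes 3.491 / √(1 − r²), where 3.491 = 0.4005 × √(940 × 0.9701 / 12) is the large-sample form of the 3.487 above.

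| assumed r | 1 − r² | statistic | power at 940 | N for 90% |
|---|---|---|---|---|
| 0 | 1.00 | 3.491 | 89.4% | 957 |
| 0.3 | 0.91 | 3.660 | 92.2% | 871 |
| 0.4 | 0.84 | 3.809 | 94.2% | 804 |
| 0.5 | 0.75 | 4.031 | 96.3% | 718 |
| 0.6 | 0.64 | 4.364 | 98.3% | 613 |
| 0.7 | 0.51 | 4.888 | 99.6% | 488 |

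**Step 3: check by simulation.** Proportional odds models with and without baseline smRSq were fitted to the same simulated trials: N = 940, odds ratio 0.67 before conditioning on baseline, no site effects, 700 runs per row, Monte Carlo error about 1 point. The first-visit distribution was assumed to be the 12-month one without deaths, rescaled. The correlation was set on a latent normal scale.

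| latent r | Spearman | without baseline | with baseline | fitted OR given baseline |
|---|---|---|---|---|
| 0 | 0.00 | 89.4% | 89.6% | 0.67 |
| 0.3 | 0.27 | 87.3% | 92.1% | 0.66 |
| 0.5 | 0.46 | 88.3% | 96.0% | 0.63 |
| 0.6 | 0.55 | 88.9% | 97.0% | 0.61 |
| 0.7 | 0.65 | 86.7% | 99.6% | 0.58 |

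The without-baseline column does not depend on r by construction, so its spread is sampling noise. The with-baseline column agrees with Step 2. The last column shows that the adjusted model estimates a different quantity: an odds ratio of 0.67 without conditioning on baseline lies further from 1 once baseline is in the model.

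**The case against.** The strongest reply is that nothing stated is wrong. The plan promises "The study is predicted to have 90% power in the analysis of both primary outcomes", Step 1 confirms this for smRSq without a baseline term, and the site-adjusted test is valid. That stands, and it limits the point to efficiency.

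Four further objections have weight.

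- **The gain rests on an unknown correlation.** True of its size. Its direction holds for any correlation above zero.
- **The simulated baseline may not resemble this trial's.** The 12-month register distribution was borrowed. The protocol article expects mostly mild to moderate disability and excludes people who cannot answer the questions or do not use BankID. Scores bunched in few categories carry less information, so the real gain may be smaller.
- **The baseline is reported after allocation.** Participant timeline {13} places allocation at least 1 week before the first visit, and the trial is open-label. This is a fair caveat, but it applies equally to baseline SIS-p, which the plan already uses, so it does not explain the difference.
- **A separate analysis plan is announced.** It is left only further details. The covariates of the primary models are stated in the article.

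A reader might also infer more than the documents support. The trial is not shown to be underpowered. Age and severity, collected among "age, sex, comorbidities, stroke characteristics and severity", are not unused: section {20b} makes them subgroup factors. Nor is one primary odds ratio marginal and the other conditional: both models condition on site and differ only in the baseline term. Finally, the remark under Primary outcome on the limited sensitivity of the smRSq concerns its use as a single primary outcome, which the plan answers by adding SIS-D8; it says nothing about covariates.

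**Conclusion.** The point holds as an unexplained and inefficient difference between the two primary models. It is worth correcting, but it threatens neither validity nor the stated power. At 940 patients, adding baseline smRSq would raise power from about 89–90% to roughly 92% at an assumed correlation of 0.3 and over 99% at 0.7. By the approximation, the sample needed for 90% power would be 9% (871 against 957) to 49% (488 against 957) smaller.

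These figures assume that the correlation lies in that range, that first-visit scores are spread much like the 12-month ones, and that the design odds ratio of 0.67 is not conditional on baseline, which is how it was calculated. If 0.67 was meant as conditional on baseline, the gain would be smaller and the unadjusted analysis would fall below 90%.

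**What to change.** Before database lock and unblinding, amend section {20a}, and the analysis plan to match, so that the 12-month smRSq proportional odds model is adjusted for site and baseline smRSq, entered as a factor or a spline. State that the resulting odds ratio is conditional on baseline as well as site, whereas the design value of 0.67 was not conditional on baseline. For both primary outcomes, note that the baseline is self-reported after open-label allocation, and report the model without the baseline term as a sensitivity analysis. If the smRSq baseline is left out on purpose, give the reason.

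The cost is a few sentences and one extra model per primary outcome. No new data are needed and the sample size does not change.

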### Interim analyses {21b}

No interim analyses are planned.

### Methods for additional analyses (e.g. subgroup analyses) {20b}

Subgroup analyses, e.g. based on age (< 65 years, 65–80 years and > 80 years), sex (male and female), stroke severity (NIHSS score; mild, 0–8 moderate, 9–15 and severe, > 15), stroke type (ischaemic vs. haemorrhagic), treatment with tissue plasminogen activator and/or thrombectomy (yes or no) and geographical region, will be conducted as complementary analyses.

### Methods in analysis to handle protocol nonadherence and any statistical methods to handle missing data {20c}

All analyses will be conducted in accordance with the intention-to-treat principle. Multiple imputation of missing data will be employed in the primary analysis using multiple imputation by chained equation (MICE) [44]. As sensitivity analyses, per-protocol analyses will be performed using data from patients with fully available data for the primary variables and no protocol violations. The per-protocol dataset will be predefined in the statistical analysis plan of the study.

### Plans to give access to the full protocol, participant-level data and statistical code {31c}

The study protocol, including statistical analyses, will be available in conjunction with the scientific publication. Upon study completion, anonymized data will also be available to the scientific community at large through publications. Moreover, any party may apply to the Chief Investigator for access to the full protocol, deidentified participant-level data and the statistical code for academic research purposes by a study collaboration request. The steering committee will govern data access.

## Oversight and monitoring

### Composition of the coordinating centre and trial steering committee {5d}

The University Hospital of Umeå is the coordinating centre where the Chief Investigator (the first author) and a trial management group (TMG) work. The coordinating centre oversees the fiscal management of the study, ethics approvals, subcontracts with other participating clinics and other financial and oversight responsibilities. The TMG consists of two research nurses, two medical engineers, two RCT coordinators and the Chief Investigator. The TMG provides daily support and troubleshooting to the local participating clinics and has a brief meeting once a week to discuss actual issues.

A trial steering committee (TSC) is composed of a national collaboration among four universities and regions in Sweden. The TSC includes an independent chairperson (the last author) and multiple independent members (coauthors), including statisticians, persons with biomedical engineering degrees, rehabilitation and trial experience and patient representatives (nonauthors). TSC responsibilities include clinical setup of the study, ongoing management, study promotion and planning for the interpretation and dissemination of results. TSC meetings were held monthly during the trial planning phase. TSC meetings will take place annually at a minimum to monitor study progress and provide public, clinical information during the active phase. Moreover, professional advice to TMG members will be provided in a timely manner via e-mail or telephone when needed. The TSC will be responsible for reviewing issues and any concerns warranting modification or termination of the study.

An advisory board consisting of three professors within the stroke field will provide supervision and feedback on the project annually to the TSC. Together with TSC, this board will ensure that the interpretation of findings is applicable to current practice.

### Composition of the data monitoring committee, its role and reporting structure {21a}

The data monitoring committee (DMC) comprises two RCT process controllers who are independent of the study sponsor and funder. The DMC will monitor clinical trial compliance, the completeness of the study data and data safety twice a year, in accordance with the Standard Operating Procedure (SOPs) and Consolidated Standards of Reporting Trials (CONSORT) statement.

### Adverse event reporting and harms {22}

Even though they are unlikely in this study, adverse events will be immediately reported to the TSC if classified as Related and Unsuspected Serious Adverse Events (RUSAEs), i.e. events that are unexpected in severity and seriousness and suspected to be related to the study intervention. The TSC will then report the case to the DMC with a tailored action plan.

### Frequency and plans for auditing trial conduct {23}

To increase the fidelity of the study, the DMC members who are independent of the sponsor will regularly (4 times while participating in the study) notify the participating clinics if there is a breach of protocol or GCP principles that is likely to significantly affect participant safety, health and wellbeing as well as the scientific value of the research.

### Plans for communicating important protocol amendments to relevant parties (e.g. trial participants, ethical committees) {25}

Important protocol amendments will be made by the Chief Investigator following consultation with the TMG and the TSC. All changes to the protocol will be reviewed and approved by the Swedish Ethical Review Authority prior to their implementation. Amendments will then be communicated to research staff and participants by the PI. The major protocol changes will be updated by the Chef Investigator in the clinicaltrials.gov and ISRCTN registry protocol registration within 14 days.

## Dissemination plans {31a}

Annual trial meetings will be organized for all unit-allied health professionals for exchanging experiences and spreading knowledge. Monthly newsletters and ongoing e-mail contact will also be used to update the study progress and facilitate communication during the study.

Upon completion of the trial, investigators will report results, regardless of the direction or magnitude of the effect, through peer-reviewed journal articles, scientific presentations, patient education websites, public media, ClinicalTrials.gov and ISRCTN registry. We endeavour to facilitate knowledge transfer and exchange among different stakeholders.

## Discussion

Stroke is a leading cause of disability among adults worldwide, with a heavy burden for patients and their families as well as society [2, 3]. Despite the recent recommendation by Swedish stroke guidelines, structured follow-up to identify patients’ rehabilitation needs and develop patient-tailored rehabilitation regimens is largely lacking in current stroke care [4]. Establishing such care, however, risks heavy encumbrances for our already time- and resource-constrained health care system. Therefore, a cost-effective and user-friendly solution is desperately needed to improve patients’ daily activities and quality of life.

To meet these challenges, Rehabkompassen® was recently created and developed as a novel and unique digital follow-up tool to identify and graphically visualize a panoramic view of stroke patients’ heterogeneous rehabilitation needs based on 6 well-validated and reliable PROMs [10, 11]. The utilization of Rehabkompassen® may facilitate the identification of rehabilitation needs among persons after stroke and therefore advance patient-tailored rehabilitation regimens and improve patients’ clinical outcomes. In addition to the intervention arm, an active control arm is planned by using the paper form of the PSC [17] as a structured follow-up tool, recommended by the Swedish National Board of Health and Welfare during clinical visits in usual care settings. This will ensure that the patients in the control group will receive equal care. Since the PSC has not been widely used in usual stroke care in Sweden, this trial could promote the usage of the PSC.

This two-arm pragmatic multisite study will be able to provide unequivocal results of the eventual effectiveness of the Rehabkompassen tool since both the intervention and control are used in normal practice. Moreover, this trial provides substantial flexibility concerning the adaptation of the Rehabkompassen tool into everyday clinical practice, such as stroke units, early support discharge units and stroke rehabilitation units, in the post-acute continuum of care after stroke in Sweden. A multicentre study also means extra attention should be given to ensure the minimization of the differences and variations among clinics. This is why we will collect baseline data concerning usual care and provide the study information and a training program on the usage of Rehabkompassen® and REDCap prior to patient recruitment. In addition, much information about implementation will be collected from medical practitioners in the participating clinics in the proposed study. Together with the high generalizability of the pragmatic trial [14], this will facilitate the future implementation of the Rehabkompassen® tool in combination with usual care as a standard structured follow-up model in the rest of the country if successful.

Despite the potential usefulness of the tool, there are various practical and operational issues to consider in this study. We are certainly aware of the major challenge of recruiting more than 1000 patients, which is required for the power analysis. Our pilot study demonstrated a recruitment rate of 28% with a retention rate of 86% at the 12-month follow-up without any severe adverse effects during the heavy pandemic period [11]. This means that we need to screen approximately 5000 stroke patients, i.e. approximately 8% of the total stroke patients in Sweden, during 3 years of recruitment. This is why we are confident that recruiting 1106 patients is still an achievable goal, especially with strong financial support from various Swedish research funding.

We are also aware of the challenge of running such a large multicentre study, especially concerning data collection and management, which is why a separate data management plan has been established and kept at Umeå University. Another issue is technical obstacles for the participants, who are often elderly since the mean age of stroke patients is 73 years old [11]. We have thus planned to have research nurses or a nurse assistant who will assist participants in overcoming technical issues in each county. Finally, the challenge of unblinding the intervention will increase the risk of spill-over effects when patients from the treatment and control groups are treated in the same clinic. GCPs, including strictly keeping the research protocol separate for the intervention and control groups, will decrease the risk of possible spill-over effects.

This study will provide strong evidence on the effectiveness and cost-effectiveness of a novel digital follow-up tool, Rehabkompassen®, in persons discharged from acute care settings after stroke. In addition to improving the tool to be more user -riendly, we envisage finding a cost-effective solution to carry out standard follow-up visits and to facilitate patient-tailored rehabilitation in persons with stroke in current clinical practice. This tool has the potential to improve everyday life for many stroke patients and to reduce the health, social and economic burdens after stroke for patients and their families as well as society. The outcomes of this trial will inform clinical practice and health care policy on the role of the digital follow-up tool Rehabkompassen® in the post-acute continuum of care after stroke.

